**Study Design: Biomedical**

**1. Will controls be used?**

Yes

**►IF YES, explain the kind of controls to be used.**

Subjects will have pre-intervention testing to determine efficacy of exercise and/or diet on insulin sensitivity and immune health.

1. **What is the study design?**

Matched pair, prospective design. Bariatric patients will be match paired to the exercise or standard medical care group. Subjects not undergoing bariatric surgery will be randomized to calorie restriction or calorie restriction + exercise groups.

1. **Does the study involve a placebo?**

No

# Human Participants

**Ages:** 18-70 years

##### Sex: Men and Women

**Race:** All

**1. Provide target # of subjects (at all sites) needed to complete protocol.**

A total of **60 subjects** will be needed to complete the study in order to determine statistically significant results.

**2. Describe expected rate of screen failure/ dropouts/withdrawals from all sites.**

Based on prior work by our group, we anticipate that 20% of subjects who receive randomization (i.e. treatment) in the study will withdraw/drop out early.

For individuals not receiving bariatric surgery, we anticipate that 30% of subjects who are initially recruited to participate in the screening visits will not meet the criteria for inclusion in the study (i.e. not passing physical examination, abnormal ECG, abnormal exercise test, abnormal blood chemistries, outside of BMI range, pregnancy). Therefore, we expect to screen 38 individuals not receiving bariatric surgery for participation in the study. Of the 38 subjects screened, 28 will undergo the treatment. Accounting for dropouts, 24 subjects will complete the study.

For individuals receiving bariatric surgery, we anticipate 20% of subjects who are initially recruited to participate in the screening visits will not meet the criteria for inclusion in the study (i.e. not passing physical examination, abnormal ECG, abnormal exercise test, abnormal blood chemistries, outside of BMI range, orthostatic intolerance). Therefore, we expect to screen 20 individuals receiving bariatric surgery for participation in the study. Of the 20 subjects screened, 16 will undergo the treatment. Accounting for dropouts, 12 subjects will complete the study.

**Thus, we expect to screen 60 subjects of whom 50 will receive treatment and 40 will complete the study.**

**3. How many subjects will be enrolled at all sites?**

We expect to enroll 60 subjects of whom 50 will receive treatment and 40 will complete the study.

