##### 4. How many subjects will sign a consent form under this UVa protocol?

A total of 60 subjects will sign the consent form.

1. **Provide an estimated time line for the study.**

We anticipate this study will take approximately 18-36 months to meet 100% enrollment. Each participant will be enrolled for a total of approximately 12 weeks from the time of screening to study completion. Our team will interact with 4-5 subjects at one time. As a result, approximately 8-12 subjects per year will be enrolled.

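### The stated totals of 60 enrolled, 50 treated and 40 completing do not follow from the protocol's own cohort counts, and 8-12 subjects a year cannot fill the study in 18-36 months

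*Protocol*

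**What the plan says.** All the participant counts are in the Protocol, under Human Participants, with the group sizes under Statistical Considerations.

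- **Item 1 (target number):** 60 subjects "will be needed to complete the study in order to determine statistically significant results".
- **Item 2 (losses), all subjects:** "we anticipate that 20% of subjects who receive randomization (i.e. treatment) in the study will withdraw/drop out early".
- **Item 2, non-bariatric cohort,** with 30% screen failure: "Of the 38 subjects screened, 28 will undergo the treatment. Accounting for dropouts, 24 subjects will complete the study".
- **Item 2, bariatric cohort,** with 20% screen failure: "Of the 20 subjects screened, 16 will undergo the treatment. Accounting for dropouts, 12 subjects will complete the study".
- **Closing line of item 2, and item 3:** the overall totals. Item 2 presents them as following from the two cohorts, and item 3 repeats them: "We expect to enroll 60 subjects of whom 50 will receive treatment and 40 will complete the study".
- **Item 4 and the time line:** 60 subjects sign consent. "We anticipate this study will take approximately 18-36 months to meet 100% enrollment", while "approximately 8-12 subjects per year will be enrolled".
- **Statistical Considerations, item 3 (sample-size justification):** after allowing for 20% dropout, 8 per group in the two bariatric groups and 14 per group in the two non-bariatric groups. Before that allowance, the numbers are 5 and 6 subjects for the bariatric calculations and 10 for the non-bariatric one.

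**The concern.** An overall line offered as the conclusion from two cohort flows should be their sum. Here the screened count is close, but the treated and completing counts are not. Item 1 then attaches the figure of 60 to completion and to statistical significance, whereas everywhere else in the section 60 counts people screened, enrolled or consented. The time line pairs a yearly rate with an enrolment period that cannot both be true for any of the totals given.

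What is at stake is the reliability of the stated size and feasibility of the study. A reader judging whether it can be finished, or how many subjects will contribute data, gets different answers from adjoining items.

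**Working it through.** **1. Sum of the cohort flows (Human Participants, item 2) against the stated totals (items 2-3).**

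| | Non-bariatric | Bariatric | Sum | Stated | Difference |
|---|---|---|---|---|---|
| Screened | 38 | 20 | 58 | 60 | 2 |
| Treated | 28 | 16 | 44 | 50 | 6 |
| Completing | 24 | 12 | 36 | 40 | 4 |

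The gap of 2 at screening is rounding. The gaps of 6 and 4 are not.

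**2. Where the stated line breaks.** Its last step reproduces: 50 × (1 − 0.20) = 40. Its first step does not: going from 60 to 50 is a loss of 10/60 = 16.7%, below both stated screen-failure rates (20% and 30%). So 50 is the figure without a source, and 40 inherits the error.

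**3. Cross-check on the treated total.** The group sizes in the sample-size justification give 2 × 8 + 2 × 14 = 16 + 28 = 44. This matches the cohort sum and not the stated 50.

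**4. Item 1's figure of 60.** The same justification, before its dropout allowance, needs at most 6 per bariatric group and 10 per non-bariatric group: 2 × 6 + 2 × 10 = 32 completers. With the allowance it needs 44 assigned. Neither is 60.

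**5. Accrual.** Subjects enrolled = yearly rate × years.

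- Lowest: 8 × 1.5 = 12.
- Highest: 12 × 3 = 36.
- Time to 60: 60/12 = 5.0 years to 60/8 = 7.5 years.
- Time to 44: 44/12 = 3.7 years to 44/8 = 5.5 years.
- Rate needed for 60: 60/3 = 20 a year over 36 months, or 60/1.5 = 40 a year over 18 months.

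Even the best combination reaches 36, short of the 44 to be treated.

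**6. One flow at the stated rates.**

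- Non-bariatric: 40 × 0.70 = 28 treated; 28 × 0.80 = 22.4 completing, or 11.2 per group.
- Bariatric: 20 × 0.80 = 16 treated; 16 × 0.80 = 12.8 completing, or 6.4 per group.
- Total: 40 + 20 = 60 consented; 28 + 16 = 44 treated; 22.4 + 12.8 = 35.2 completing.

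About 11 and 6 completers per group meet the 10 and the 5-6 that the protocol says it needs.

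**The case against.** The strongest reply is that these are forecasts and that the power statements do not rest on the overall totals. The second part stands. The sample-size justification works per group, and its numbers are met both at the protocol's own cohort counts (12 and 6 completers per group) and at its stated rates (about 11 and 6). A reader might infer that the wrong totals undermine the power calculation; on the protocol's own terms they do not. Whether that calculation is sound is a separate question.

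The first part stands only for the small differences: 58 against 60 screened, 38 × 0.70 = 26.6 against 28 treated, and 28 × 0.80 = 22.4 against 24 completing are near rounding. It does not cover 50 against 44, which has no source in the document.

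Item 1 can also be read more kindly. It answers a form prompt and may mean that 60 people must enter for the study to be finished. On that reading its conflict with 40 completers disappears. Steps 1-3 and 5 above remain.

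Other inferences should be resisted:

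- **Three rival targets, so that the trial could be closed at 36, 40 or 60 completers.** The 36 is a sum and is not stated anywhere, 40 is an expected yield, and no section ties the end of recruitment to a completer total.
- **A cap of 60 consents that makes 60 completers impossible.** The protocol says that 60 will sign; it does not state an approved ceiling.
- **A conflict between the yearly rate and handling 4-5 subjects at once for about 12 weeks.** That capacity gives 52/12 × 4 = 17 to 52/12 × 5 = 22 a year only if every place is refilled at once, so it is a ceiling, and 8-12 can lie below it.

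**Conclusion.** The point holds as a correction of stated totals and of feasibility. The treated total is overstated by 6 (50 against 44) and the completer total by 4 (40 against 36, or about 35 at the stated rates). Item 1's wording is wrong if 60 means completers and loose if it means enrolled; on either reading, the sample-size justification does not derive 60. The accrual conflict is the larger one: at the stated rate the enrolment period yields 12-36 subjects, and reaching 60 takes at least 60 months against a stated maximum of 36.

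This assumes that the overall line is meant as the sum of the two cohorts, as its placement and phrasing indicate, and that the yearly rate covers both cohorts together. If the rate counted only those who start treatment, 44 would still take 44-66 months. The per-group requirements remain met, so no effect on the protocol's power statements or analysis is shown.

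**What to change.** Under Human Participants:

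1. Replace the totals in items 2-3 with one flow at the stated rates: 60 consented (40 non-bariatric, 20 bariatric), 44 treated (28 and 16), about 35 completing (about 22 and about 13).
2. Adjust the cohort counts in item 2 to match, applying the same 20% dropout to both cohorts: non-bariatric screened from 38 to 40 and completing from 24 to about 22; bariatric completing from 12 to about 13.
3. Reword item 1 to say that 60 is the number consented, and refer to the sample-size justification for the per-group numbers needed.
4. Restate either the yearly rate or the enrolment period. For 60 consented, 8-12 a year means 60-90 months; keeping 18-36 months means 20-40 a year. The sponsor should choose whichever it can support.

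The cost is protocol wording and less favourable stated figures. No patients are added, the 60 consents stay, and the group sizes are unchanged.

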##### 4. How many subjects will sign a consent form under this UVa protocol?

A total of 60 subjects will sign the consent form.

1. **Provide an estimated time line for the study.**

We anticipate this study will take approximately 18-36 months to meet 100% enrollment. Each participant will be enrolled for a total of approximately 12 weeks from the time of screening to study completion. Our team will interact with 4-5 subjects at one time. As a result, approximately 8-12 subjects per year will be enrolled.

# Inclusion/Exclusion Criteria

**1. List the criteria for inclusion**

- Males and Females, 18-70 years of age
- BMI >30 and <70 kg/m^2^
- Sedentary (Not currently participating in exercise training: >30 min. of physical activity per day, >3 days/week)
- HCT for women > 36%, Men >38%
- Non-pregnant (women).-self reported
- Smoker (if bariatric surgery patient) or non-smoker (enrolled for the dietary portion of the study)
- Has the ability/willingness to participate in the study and agree to any of the arms involved in the study.
- No prior surgical procedure for obesity with the exception of a laparoscopic adjustable gastric banding (LAGB) under the condition that the band had not been adjusted in ≥ 1 year

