# Brief Summary/Abstract

Obesity is a major health concern that has been associated with an estimated 2.8 million deaths worldwide each year. The number of individuals considered obese with a Body Mass Index (BMI) above 30 kg/m^2^ has grown to more than 500 million. The increased morbidity and mortality associated with obesity stems from a long list of comorbidities, including hypertension, coronary artery disease, stroke, cancer, and type 2 diabetes (T2D). Bariatric surgery is an emerging intervention that has been used frequently to induce weight loss for obese individuals and it has been shown to improve glycemic control and insulin resistance in people at risk for type 2 diabetes. Beyond weight loss and improved glycemic control, surgery may lead to healthy improvements in inflammation, immune cells and vascular health. It is already known that exercise and weight loss from lifestyle modification can improve glycemic control, insulin resistance, levels of inflammatory cytokines, gut bacteria and arterial stiffness. However, no work has been done to examine a combination of bariatric surgery and pre-surgery lifestyle modification with diet and exercise. Recent work by our team has evidence demonstrating that health status pre-surgery has an impact on post-surgery outcomes. Such findings suggest that improvements in health status from exercise and/or caloric restriction before surgery may improve surgery outcomes as well as surgery-induced health outcomes. To date, no study has systematically examined the role of diet and/or exercise on the prevalence of surgery complications or on post-surgery weight loss, glycemic control, and insulin resistance. Moreover, no work currently exists with lifestyle modification, with or without bariatric surgery on adipose tissue derived inflammation related to immune cells or gut bacteria. Therefore, the purpose of this study is to investigate the effect of pre-surgery lifestyle intervention with diet and/or exercise on bariatric surgery outcomes. To test this objective, subjects will participate in a match paired study, based on BMI. Subjects will undergo testing of blood chemistry and related measures of health before and after lifestyle intervention, as well as 4 weeks post-bariatric surgery. The subjects will be match paired to standard care or exercise until these interventions are filled. Once standard care and exercise interventions are full subjects will then be match paired to exercise plus diet and then diet last. After the intervention all subjects will receive surgery. Post surgery outcomes will be assessed by examining surgery operating time, changes in blood chemistry, adipose tissue biopsies and other measures indicative of glucose and vascular health.

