**2. List the criteria for exclusion**

- Currently participating in exercise training: >30 min. of physical activity per day, >2 days/week)
- Cigarette smoking (presently or in the past 6 months), drug or alcohol abuse
- Pregnancy or breastfeeding
- History of congestive heart failure, ischemic heart disease, severe pulmonary disease.
- History of cancer (within 5 years)
- Diagnosed as insulin-dependent diabetes.
- Change in psychotropic medication dosage in past six weeks
- AST or ALT > 3 times normal range
- Currently involved in any active weight loss treatment program (other than self-directed attempt at calorie restricting diet) or lean patients (BMI <29 kg/m^2^).
- Current purging behavior occurring > once a week over the past six weeks (self-induced vomiting for weight control purposes, laxative or diuretic abuse)
- Revisional bariatric procedures including a RYGB reversal to a SG or a LAGB revision to a SG or RYGB if the band has been adjusted in ≤ 1 year.
- Active psychotic illness, including bipolar affective disorders.
- Evidence of current suicidality or homicidality
- Conditions associated with significant cognitive dysfunction (e.g. dementia) or medical instability that puts the participant at risk
- Contraindication to exercise (severe/uncontrolled CVD; inability to walk 2 blocks, bone or joint problems )
- Allergy to “caine” family drugs (e.g. lidocaine).
- Currently taking active weight suppression medication (e.g. phentermine,bupropion SR, topiramate).
- On medication known to cause substantial weight gain (e.g. atypical antipsychotics such as olanzapine, sodium valproate, steroid therapy). This would not include medications commonly used in this population that usually result in only mild weight loss (e.g. SSRIs).

**3. List any restrictions on use of other drugs or treatments**.

- Medication or food supplement known/thought to affect insulin sensitivity or endothelial function (TZDs, sufonylureas, biguanides, alpha-glucosidase inhibitors, phosphodiesterase inhibitors, beta-blockers, alpha-blockers, ACE-inhibitors, ARB’s, fibrates, glucocorticoids, fish oil, allopurinol, Vitamin E, Vitamin C).
- Subjects cannot ingest medications or food supplements (e.g. statins, dietary supplements, etc.) 24 hours before testing.
- Subjects cannot drink alcohol 24 hours before testing.
- Subjects cannot eat or drink foods that contain caffeine 24 hours before testing.

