# Statistical Considerations

1. **Is stratification/randomization involved?**

No. Subjects will be match paired.

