**Outcome assessments pertaining to the primary objective:**

- 1. Assess the absolute mean difference in the 3-hr postprandial glucose AUC between the 2 different conditions undergoing bariatric surgery and the 2 different groups not undergoing bariatric surgery.
  2. Assess the absolute mean difference in the 3-hr postprandial insulin AUC between the 2 different groups undergoing bariatric surgery and the 2 different groups not undergoing bariatric surgery.
  3. Compare the postprandial insulin sensitivity across conditions (as measured by the insulin sensitivity index- ISI; a calculated value based on the glucose/insulin values obtained from the MMTT or OGTT)
  4. Compare the mean change in body fat between groups.
  5. Compare the mean change in body weight between groups.
  6. Assess the change in cardiorespiratory fitness between groups.
  7. Determine and compare the immunophenotype from blood between groups.
  8. Relate the insulin sensitivity responses to the immunophenotyping from blood via correlations.
  9. Relate the pulse wave velocity responses to the insulin sensitivity and immunophenotyping under each condition by calculating a 3-hour pulse wave velocity AUC.
  10. Relate the augmentation index responses to the insulin sensitivity and immunophenotyping under each condition by calculating a 3-hour pulse wave velocity AUC.

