**3. Provide a justification for the sample size used in this protocol.**

*No prior work has studied adipose immune cell health in bariatric patients before or after surgery or in response to Ex+CR.* As a result, data collected in the proposed study will serve as preliminary work to determine power analysis for future studies and NIH proposed grants.

Nonetheless, the appropriate sample size required for significant differences following Ex+CR testing and surgery was, however, determined from our preliminary work (6, 11) on insulin resistance given it’s direct relation to adiposity-related immunity. A delta of 2 (Pre = 3.5 vs. Post = 5.5 surgery), SD of 1.2 with 80% power and an alpha of 0.05 indicates that **5** subjects are needed to show insulin resistance differences post-surgery, which is consistent with Ex+CR reducing insulin resistance in **6** people (Pre = 2.5 vs. Post = 4.9), SD of 1.5 at 80% power. **Thus, assuming a 20% dropout rate, 8 are required per group** **undergoing bariatric surgery.**

In contrast, subjects undergoing diet+exercise vs. diet intervention will require more subjects. This is based on an diet+exercise published study (43) on insulin resistance and energy deficit (i.e. weight loss). A delta of 3.1kg (Exercise = 3.7kg vs. Exercise+diet = 6.8kg), SD of 3.1kg with 80% power and an alpha of 0.05 indicates that **10** subjects are needed to show energy deficit differences. **Thus, assuming a 20% dropout rate, 14 will be required per group** **NOT undergoing bariatric surgery.**

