  - Federal regulations allow the UVa Health System to release your information to researchers at UVa, so that we may contact you regarding studies you may be interested in participating. We want to assure you that we will keep your information confidential.
- IF THE PERSON SEEMS ANGRY, HESITANT OR UPSET, THANK THEM FOR THEIR TIME AND DO NOT ENROLL THEM IN THE STUDY. YOU MAY ALSO REFER THEM TO THE IRB-HSR AT [name].

c.____Direct contact of potential subjects by the study team by approaching in person at UVa or via letter, phone, direct e-mail. Members of study team contacting potential subjects ARE health care providers of patients.

If you are not approaching them in person but using a letter, phone call or direct email please note that the letter, phone, direct email scripts must be approved by IRB prior to use.

See [IRB-HSR Website](http://www.virginia.edu/vpr/irb/hsr/advertising.html) for templates.

DHHS: Study team requests a Waiver of Consent to contact potential subjects

HIPAA: Allowed under Health Care Operations.

d.__X__ Indirect contact (flyer, brochure, TV, broadcast emails, patient provided info about the study from their health care provider and either the patient contacts study team or gives their healthcare provider permission for the study team to contact them.)

The indirect method used (flyer, brochure, TV, broadcast emails) must be approved by the IRB prior to use. The IRB does not need to review any type of script to use when the potential subject responds to the indirect method.

DHHS & HIPAA: NA

1. ____ Potential subjects are not patients. The study does not include obtaining subjects health information. Subjects will be contacted directly via email, phone, letter or presentation in group setting with consent then obtained individually in a private setting.

If you are not approaching them in person but using a letter, phone call or direct email please note that the letter, phone, direct email scripts must be approved by IRB prior to use.

See [IRB-HSR Website](http://www.virginia.edu/vpr/irb/hsr/advertising.html) for templates.

DHHS: Study team requests a Waiver of Consent to contact potential subjects.

HIPPA: NA

1. **Will any additional information be obtained from a potential subject during "prescreening"?**

Yes. The list of prescreening questions will be asked as follows:

1. Do you smoke, or have you smoked in the last 6 months?
2. What is your weight and height?
3. Do you have normal mensuration?

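### The smoking criterion for the bariatric cohort contradicts itself: the inclusion list admits smokers, and the exclusion list bars cigarette smoking without exempting that cohort

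*Protocol*

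**What the plan says.** Under Inclusion/Exclusion Criteria, item 1 (inclusion), one bullet gives smoking status by cohort: "Smoker (if bariatric surgery patient) or non-smoker (enrolled for the dietary portion of the study". Item 2 (exclusion) lists "Cigarette smoking (presently or in the past 6 months), drug or alcohol abuse" as a single bullet for all subjects. It does not mention the bariatric cohort, either to include or to exempt it.

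The prescreening questions in Appendix: Recruitment ask every potential subject "Do you smoke, or have you smoked in the last 6 months" and attach no rule for using the answer in either cohort.

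On allocation, the Brief Summary says that "subjects will participate in a match paired study, based on BMI", and BMI is the only matching factor it names. Statistical Considerations, item 1, answers the question on stratification or randomization with "No. Subjects will be match paired". The sample size justification states that "8 are required per group" for the patients having surgery.

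**The concern.** Eligibility lists often overlap untidily, and applying the stricter rule usually resolves it. Here the stricter rule cancels text that was written on purpose. The inclusion bullet separates the two cohorts and gives the surgical one a different smoking status, so its author evidently meant the rules to differ. The exclusion bullet takes no account of that difference.

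Two coordinators following the same protocol could therefore decide differently about the same patient, and each could be cited for a violation of the other list. The exercise and standard-care groups are small and matched rather than randomized, so a few admissions either way change who is being studied. Smoking could plausibly bear on outcomes the protocol plans to examine, such as "Determine and compare the immunophenotype from blood between groups" and the surgical complications in Primary Objective 2. The protocol does not itself say that smoking affects these outcomes; that link is general reasoning.

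**Working it through.** The contradiction is textual, so the check is to take each type of candidate through both lists.

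| Candidate | Inclusion bullet | Exclusion bullet | Result |
|---|---|---|---|
| Bariatric, smokes cigarettes | met | triggered | conflict |
| Bariatric, non-smoker | not met if read literally | not triggered | eligible only if the bullet is read as permission |
| Non-bariatric, smokes cigarettes | not met | triggered | excluded by both lists |
| Non-bariatric, non-smoker for over 6 months | met | not triggered | eligible under both lists |

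The last two rows agree across the lists; the first two do not. Read literally and together, the lists would admit neither cigarette-smoking nor non-smoking bariatric patients, which cannot be intended.

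Three readings might reconcile the bullets:

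1. The exclusion overrides. This is workable, but the bariatric half of the inclusion bullet then does nothing.
2. The exclusion was meant for the non-bariatric cohort only. This is plausible, but it is not written.
3. The inclusion bullet means people who smoke something other than cigarettes, or who stopped long ago. This is not written either.

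The protocol has no figure of its own to reproduce. What follows is an illustration of what admitting smokers could mean for balance.

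- Inputs: n = 8 per bariatric group (sample size justification). Smoking prevalence p is not given; 0.1 to 0.3 is assumed.
- Model: the numbers of smokers X and Y in the two arms are independent Binomial(n, p), with no matching on smoking.
- Formula: P(|X − Y| ≥ 2) = 1 − P(X = Y) − P(|X − Y| = 1).

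| p | P(X = Y) | P(difference of 1) | P(difference of 2 or more) |
|---|---|---|---|
| 0.1 | 0.355 | 0.454 | 0.19 |
| 0.2 | 0.251 | 0.410 | 0.34 |
| 0.3 | 0.216 | 0.374 | 0.41 |

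Two smokers among 8 is 2/8 = 25 percentage points. The Human Participants section expects 16 bariatric patients to start and 12 to complete. Assuming 12/2 = 6 completers per arm, the same formula gives 0.13, 0.27 and 0.34, and a gap of two is 2/6 = 33 percentage points.

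These probabilities count imbalance in either direction. They do not measure a shift in any outcome, and they apply only if smokers are admitted.

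**The case against.** The strongest reply is that a subject must meet every inclusion criterion and no exclusion criterion, so smokers are simply out. That reading exists, and a reader should not infer that no stricter rule is available. Its weakness is that it empties a cohort-specific clause, so staff cannot be sure that it is the intended one.

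Four further inferences are tempting, and the protocol does not support them.

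- *Bariatric smokers are expressly excluded, or the bariatric population is undefined.* The exclusion is a blanket bullet that never names these patients, and only their smoking status is unclear.
- *The prescreening question adds to the contradiction.* It is neutral. Staff need the answer under either rule, and the recruitment appendix limits such questions to those that bear on eligibility. The script needs no repair.
- *Smoking imbalance would bias the exercise versus standard-care comparison.* The planned analysis is a repeated measures ANOVA of group by test. A stable difference in level between smokers and non-smokers falls in the between-subject part. Bias in the group-by-time term would require smoking to alter the response, or to change during follow-up. The vascular item, "Relate the pulse wave velocity responses to the insulin sensitivity and immunophenotyping", is a correlation within conditions and not a contrast of arms. The argument is stronger for surgical complications, which have no baseline value.
- *Smoking should become a second matching factor.* With about 16 patients this may be impractical, and its absence is not an error. Tables with and without smokers are the kind of detail a protocol may leave to the statistical analysis plan, and they would tell little with so few smokers: 8 × 0.1 = 0.8 to 8 × 0.3 = 2.4 expected per arm.

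None of this removes the conflict between the two bullets.

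**Conclusion.** The point holds as an eligibility rule that contradicts itself. For a bariatric candidate who smokes, the protocol gives opposite answers in two adjacent lists and offers nothing to choose between them. The defect is limited to one criterion in one cohort, 16 planned patients in two groups of 8; the non-bariatric cohort is unaffected.

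This conclusion rests on the wording alone and on no assumption about smoking rates. The imbalance probabilities (0.19 to 0.41 with 8 per arm, 0.13 to 0.34 with 6) are illustrative, depend on the assumed prevalence of 10–30%, and do not show that any result would be biased. The correction should be made because it decides who enters and costs little.

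**What to change.** Amend the two smoking bullets so that one explicit rule applies to each cohort, with any look-back window stated in the same terms in both lists. The sponsor decides which rule applies to bariatric patients.

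- If bariatric smokers are to be admitted: confine the exclusion bullet to the non-bariatric cohort, reword the inclusion bullet so that smoking is permitted rather than required, and record smoking status at entry. Reporting the number of smokers by arm is optional and would be most useful beside surgical complications.
- If they are to be excluded: delete the bariatric clause from the inclusion bullet and leave the exclusion as it is.

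The prescreening script and the BMI matching can stay as they are. The cost is one wording amendment. Admitting smokers adds one recorded item, which prescreening already asks about; excluding them may slow recruitment slightly.
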